## Abstract

**Background:**

Flying phobia (FP) is a common and disabling mental disorder. Although in vivo *exposure* is the treatment of choice, it is linked to a number of limitations in its implementation. Particularly important, is the limited access to the feared stimulus (i.e., plane). Moreover, the economic cost of in vivo *exposure* should be specially considered as well as the difficulty of applying the exposure technique in an appropriate way; controlling important variables such as the duration of the exposure or the number of sessions. ICTs could help to reduce these limitations. Computer-assisted treatments have remarkable advantages in treating FP. Furthermore, they can be delivered through the Internet, increasing their advantages and reaching more people in need. The Internet has been established as an effective way to treat a wide range of mental disorders. However, as far as we know, no controlled studies exist on FP treatment via the Internet. This study aims to evaluate the efficacy of an Internet-based treatment for FP (*NO-FEAR Airlines*) versus a waiting list control group. Secondary objectives will be to explore two ways of delivering *NO-FEAR Airlines*, with or without therapist guidance, and study the patients’ acceptance of the program. This paper presents the study protocol.

**Methods/design:**

The study is a randomized controlled trial. A minimum of 57 participants will be randomly assigned to three conditions: a) *NO-FEAR Airlines* totally self-applied, b) *NO-FEAR Airlines* with therapist guidance, or c) a waiting list control group (6 weeks). Primary outcomes measures will be the *Fear of Flying Questionnaire-II* and the *Fear of Flying Scale*. Secondary outcomes will be included to assess other relevant clinical measures, such as the *Fear and Avoidance Scales*, *Clinician Severity Scale,* and *Patient’s Improvement scale*. Analyses of post-treatment flights will be conducted. Treatment acceptance and preference measures will also be included. Intention-to-treat and per protocol analyses will be conducted.

**Discussion:**

An Internet-based treatment for FP could have considerable advantages in managing in vivo *exposure* limitations, specifically in terms of access to treatment, acceptance, adherence, and the cost-effectiveness of the intervention. This is the first randomized controlled trial to study this issue.

**Trial registration:**

Clinicaltrials.gov: NCT02298478. Trial registration date 3 November 2014.

**Electronic supplementary material:**

The online version of this article (doi:10.1186/s12888-016-0996-1) contains supplementary material, which is available to authorized users.

## Background

Flying Phobia (FP) is a common and disabling disorder classified as a situational specific phobia [1]. The symptoms of FP can encompass several diagnostic categories (such as panic disorder, agoraphobia, claustrophobia, or acrophobia), making diagnosis and treatment complex [2, 3]. Recent studies have established a lifetime prevalence of approximately 2.5 % of the adult population [4], although previous epidemiological studies reported prevalence estimates ranging from 10 to 40 % [5, 6]. Moreover, research has pointed out that around 25 % of the adult population suffers from anxiety when taking a flight, about 10 % avoid flying due to the intensity of their fear, and approximately 20 % depend on alcohol or anxiolytics to fly [7].

Consequences of FP are far-reaching, resulting in substantial social costs from the patient’s perspective, which for some authors are incalculable [8], as well as the costs for aeronautical companies [9, 10]. Interference caused by this problem is diverse and varies depending on personal demands or needs, as well as patients’ geographical location. According to Busscher et al. [2], 7 % of the population experience serious interference in daily life and social functioning due to FP. Personal consequences of suffering from FP may consist of limited professional opportunities or leisure options and changing or disrupted relationships, and it often causes shame and emotional distress when the person faces the thought of flying [4, 11, 12].

There are evidence-based psychological interventions for FP [13, 14], and the most effective treatment approach for this problem is in vivo *exposure* [4]. Studies report that more than 90 % of participants whose treatment included in vivo *exposure* continued to fly at one- to four-year follow-up [14]. However, this technique is linked to a number of limitations in its implementation, related to access and acceptance by patients and therapists [15]. With regard to treatment accessibility, most people suffering from phobias never seek help [16], only 7.8 % search for a treatment [17], and only 8 % of patients receive a specific treatment for their problem [18]. There could be several reasons for this, such as long waiting lists, lack of evidence-based treatment offered by healthcare systems, and insufficient therapist training to apply the exposure technique [19–21]. As for patients’ acceptance of in vivo exposure, around 25 % reject the treatment when they are informed about the procedure, or they drop-out during treatment [15, 22]. In addition, some authors have considered exposure to be a cruel cure, inhumane, and ethically inappropriate [15, 23]. Furthermore, in vivo exposure involves lack of confidentiality or high associated costs when it has to be conducted outside the therapist’s office [13]. And, finally, but particularly important in FP, is the limited access to the feared stimulus (i.e., airport or plane) [24]. Moreover, for this specific phobia the economic cost of in vivo exposure should be specially considered as well as the difficulty of applying the exposure technique in an appropriate way; that is, controlling important variables such as the duration of the exposure or the number of sessions.

According to Kazdin [21], there is a need for new models to deliver mental health and reduce the burdens of mental illness. In the case of FP treatment, it is necessary to improve exposure therapy in terms of adherence and acceptance, and help to reach a higher number of patients than with traditional face to face therapy. Information and Communication Technologies (ICTs) can be useful in this endeavor. Specifically, Computer-assisted treatments such as virtual reality exposure therapy (VRET) and computer-assisted exposure have noteworthy advantages in treating FP. Some of these advantages are: providing an intermediate step between the therapist’s office and the real world; the possibility of standardizing treatment as much as possible with a steep exposure gradient; its low cost and accessibility for patients who would not be very willing to subject themselves to live exposure (a real flight); a reduction in direct therapeutic contact time; confidentiality compared to in vivo exposure conducted in a public place; and better acceptance by patients and therapists because it evokes lower anxiety levels [13, 25–27].

VRET has been shown to be effective for FP treatment in several meta-analyses and systematic reviews [28–31]. Regarding computer-assisted exposure programs for FP, the literature shows only one system that has efficacy data. Bornas et al. (2001) developed a computer-assisted exposure program (*Computer Assisted Fear of Flight Treatment, CAFFT)* that has been shown to be effective in several studies [27, 32]. In this regard, Tortella-Feliu et al. [32] pointed out that the *CAFFT program* (with therapist presence and self-administered in the lab) and a VR system [7] equally reduced FP outcomes at post-treatment and 1-year follow-up. These data suggest that less sophisticated and cheaper devices might be sufficient to produce satisfactory outcomes.

On the other hand, this type of computer-assisted treatment can be delivered through the Internet, which would improve the advantages of this way of applying exposure, reaching more people in need. The Internet has been shown to be an effective tool for treating a broad range of psychological disorders and psychiatric conditions, particularly depression and anxiety disorders [33–35], and it can address common treatment barriers such as limited access to mental health treatments [35]. Specifically, authors have pointed out five main advantages: efficacy, effectiveness, safety, geographical reach, acceptability, and convenience [36]. However, according to Andersson [33], in spite of the fact that specific phobias are common, only two studies with self-help Internet-based programs have been published, one on spider phobia [37] and one on snake phobia [38].

However, despite the proven efficacy of these programs, there are still some questions that remain unclear, such as the impact of clinician guidance. To date, evidence shows that guidance is a beneficial feature that leads to better adherence and better outcomes in programs administered through the Internet [34, 39–41]. Nevertheless, other authors have shown that unguided self-help interventions are useful alternatives with similar outcomes that might work using automated reinforcement [40, 42, 43]. Moreover, the results so far indicate a small but significant effect size of these self-help interventions compared to a control condition [43–47]. Therefore, more research is needed to examine and determine critical key aspects of clinician guidance that promote positive effects [36].

In sum, the Internet is a useful and effective tool for providing psychological treatments, and there is a large body of research about this topic. However, no published study has explored these issues in the research on FP. As far as we know, no controlled FP study has been published to test the efficacy of an Internet-based treatment.

The purpose of the randomized control trial (RCT) described in this study protocol is to investigate the effectiveness of an Internet-based exposure treatment for FP (*NO-FEAR Airlines*) versus a waiting list control group. Secondary objectives are: a) to explore two ways of delivering *NO-FEAR Airlines*, with or without therapist guidance, and b) to study the patients’ acceptance through expectations, preferences, and satisfaction with the online program. This paper presents the study design.

## Methods/design

### Study design

A three-armed simple-blind RCT will be conducted. Participants will be randomized into three groups: 1) Internet-based exposure treatment for FP without therapist guidance (*NO-FEAR Airlines* totally self-applied); 2) Internet-based exposure treatment for FP with therapist guidance (brief weekly call) (*NO-FEAR Airlines* with therapist guidance); and 3) a waiting list control group. Participants in the control group will be randomly assigned to one of the two treatment conditions after spending time on the waiting list (6 weeks) for ethical reasons. The study was registered under clinicaltrials.gov (NCT02298478) and will be conducted following the CONSORT statement (Consolidated Standards Of Reporting Trials, http://www.consort-statement.org), the CONSORT-EHEALTH guidelines [48] and the SPIRIT guidelines (Standard Protocol Items: Recommendations for Interventional Trials) [49, 50]. SPIRIT checklist (http://www.spirit-statement.org/spirit-statement/) was followed for the reporting of the present study protocol (Additional file 1). Figure 1 shows the flowchart for the study.

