### Recruitment, randomization and blinding

The study will be advertised online via professional websites (i.e., LinkedIn), non- professional social-networks (i.e., Facebook and twitter), and advertisements in newspapers. Furthermore, posters will be placed in local universities (Universitat Jaume I and Universitat de València) and travel agencies. People who are interested will be directed to the research website (www.fobiavolar.es), where they will find further information about the study and what participation entails, as well as an informed consent form. Individuals can request participation through the website and by signing the informed consent form. After website registration, the clinical team will contact participants by telephone to screen for the inclusion and exclusion criteria and explain the research terms (i.e., study design, treatment length, or treatment rationale). Participants who meet the criteria will be administered a diagnostic telephone interview at the time of the screening, or another time will be arranged. Then, participants will be randomly assigned to one of the three experimental groups. The allocation schedule will be generated through a computer randomization program (Epidat 4.0) by an independent researcher who will be unaware of the characteristics of the study. The allocation schedule will be communicated to the study researchers via phone call. Patients will agree to participate before the random allocation and without knowing to which treatment they will be assigned. However, for practical reasons, participants and researchers will not be blind to the treatment conditions. Participants will be free at any time to withdraw from the treatment or the study without giving any explanation.

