### Instruments

Participants will be assessed at baseline, post-treatment, and 3- and 12-month follow-ups. Assessments will be conducted via call phone, a commercial online survey system (www.surveymonkey.com), and the *NO-FEAR Airlines* program. Both participants and therapists will receive email reminders of each assessment time. The study variables and assessment times are summarized in Table 1.

**Table 1 Tab1:** Study measures, time of assessment, and source of measurement

Measures	Aim	Time of assessment	Source of measurement
ADIS-IV	Diagnosis	BL, post-T and FU	Phone Call
Sociodemographic data	Gender, age, education, occupation, marital status	BL	
FFQ-II	Severity of the FP	BL, post-T and FU	*NO-FEAR Airlines*
FFS	Severity of the FP	BL, post-T and FU	Phone Call
Fear and Avoidance Scales	Fear avoidance, and the degree of belief in catastrophic thought related to the main target behavior.	BL, post-T and FU	Phone Call
Clinician Severity Scale	severity of the patient’s phobia	BL, post-T and FU	Clinician
Patient’s Improvement Scale	Patient’s improvement assessment	BL, post-T and FU	Phone Call
Treatment Preferences Questionnaire	Participant’s treatment preferences	BL, post-T and FU	Phone Call
ESQ	Expectations and satisfaction with the treatment	BL, post-T and FU	Phone Call
*Measures related to flying phobia*	Duration of the problem, flights taken, Safety behaviors, presence of negative experience flying.	BL, post-T and FU	*NO-FEAR Airlines*
Anxiety during exposure	Maximum level of anxiety experienced during the exposure scenarios	During exposure scenarios	*NO-FEAR Airlines*
Cycles of exposure scenarios	Number of cycles in each exposure scenario	After exposure scenarios	*NO-FEAR Airlines*

*BL* Baseline, *Post-T* post-treatment, FU, 3- and 12-month follow-ups; *ADIS-IV* The Anxiety Disorders Interview Schedule for DSM-IV-TR; *FP* Flying phobia, *FFQ-II* Fear of Flying Questionnaire-II, *FFS* Fear of Flying Scale, *ESQ* Expectations and satisfaction Questionnaire

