#### Primary outcomes

The Fear of Flying Questionnaire-II (*FFQ-II*) [58] is a 30-item self-report instrument that describes situations related to flying: anxiety during flight, anxiety experienced getting on the plane, and anxiety experienced during the observation of neutral or unpleasant flying-related situations. For each item, respondents rated their degree of discomfort associated with the situation on a scale from 1 to 9 (1 = not at all, 9 = very much). Scores ranged from 30 to 270. As reported by Bornas et al. [58], internal consistency was *α* = .97, and retest reliability (15-day retest period) was *r* = .92.

The Fear of Flying scale (*FFS*) [59] is a 21-item self-report measure to assess fear associated with various air travel situations. Fear elicited by each situation was rated on a 5-point scale (0 = *not at all*, 4 = *very much*), with scores ranging from 0 to 84. For the original FFS [59], Cronbach’s alpha was .94, and retest reliability (at three months) was .86.

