##### Other relevant clinical measures

Fear and Avoidance Scales (adapted from Marks & Mathews [60]) are used to assess participants’ fear and avoidance on a scale ranging from 0 (“No fear at all,” “I never avoid”) to 10 (“Severe fear,” “I always avoid”) related to the main target behavior: “flying”. The degree of belief in the catastrophic thought related to the target behavior will also be assessed on a 0 (“*I do not believe the thought at all*”) to 10 (*the thought is totally true*) scale.

The Clinician Severity Scale (adapted from Di Nardo, Brown & Barlow [61]). The clinician rates the severity of the patient’s phobia on a scale from 0 to 8, where *0 = symptom free* and *8 = extremely severe.*

The Patient’s Improvement Scale (Adapted from the Clinical Global Impression scale, CGI; Guy [62]). One item on the CGI scale was adapted in order to assess the level of improvement achieved by the patient (compared to the baseline status) on a 7-point scale (1 “much worse” to 7 “much better”). This scale is answered by the patient.

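### The trial is labelled simple-blind, but no one is described as blind to the assigned arm, and one of the two self-report primary outcomes is collected by telephone

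*Protocol article*

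**What the plan says.** The protocol article makes two statements about blinding. Under Study design: "A three-armed simple-blind RCT will be conducted". Under Recruitment, randomization and blinding: "However, for practical reasons, participants and researchers will not be blind to the treatment conditions".

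The only person described as unaware of anything is the one who prepares the randomization. The schedule is generated "by an independent researcher who will be unaware of the characteristics of the study". Then "The allocation schedule will be communicated to the study researchers via phone call".

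On outcome collection, the FFS is one of two primary outcomes and "is a 21-item self-report measure to assess fear associated with various air travel situations". Table 1 gives its source as a phone call at baseline, post-treatment and follow-up. The other primary outcome, the FFQ-II, is collected by the treatment program. The ADIS-IV, the Fear and Avoidance Scales and the Patient's Improvement Scale are also phone calls. For the Clinician Severity Scale, "The clinician rates the severity of the patient’s phobia on a scale from 0 to 8".

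The Instruments section begins "Assessments will be conducted via call phone, a commercial online survey system" and adds the program as a third route. Table 1 assigns no measure to the survey system.

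**The concern.** A single-blind label tells the reader that some party, usually the participant or the outcome assessor, does not know the allocation. Here participants must know whether they are waiting, working alone or receiving weekly calls, so the label could only refer to assessors or analysts. The article names neither, and it says that researchers are not blind. A reader who relies on the Study design section would credit the trial with a protection that the later section denies.

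The point has practical weight because of how one primary outcome is obtained. If a caller who knows the arm takes a fear scale from the participant, the answers may be influenced by that contact. In the guided arm, participants will also have had up to six support calls giving feedback and reinforcement, so the influence need not be equal across arms. That would affect guided versus unguided delivery, a stated secondary objective, as well as each active arm against the waiting list.

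**Working it through.** No figure in the plan depends on the blinding label, so this is a comparison of text.

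**1. Who could be blind?**

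| Party | What the article says | Blind to the assigned arm? |
|---|---|---|
| Participants | Not blind (Recruitment, randomization and blinding) | No |
| Researchers | Not blind (same sentence, no exception) | No |
| Independent researcher who generates the schedule | Unaware of the study's characteristics | Concerns sequence generation; no part in outcome assessment is described |
| Outcome assessor or caller | Not named | No blinding described |
| Analyst | Not named | No blinding described |

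No row supports the label.

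**2. How is each measure collected?** Table 1 has 12 rows. Six are phone calls (ADIS-IV, FFS, Fear and Avoidance Scales, Patient's Improvement Scale, Treatment Preferences Questionnaire, expectations and satisfaction). Four come from the program (FFQ-II, measures related to flying phobia, anxiety during exposure, cycles). One is rated by the clinician and one has no source: 6 + 4 + 1 + 1 = 12. Of the two primary outcomes, one (FFS) is taken by phone and one (FFQ-II) is not.

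**3. Does the caller know the arm?** This is inference, because no section names the person who makes the outcome calls. Four statements point the same way:
- researchers are unblinded without exception;
- the clinical team makes the screening calls;
- therapists receive the reminders of each assessment time (Instruments);
- the expectations scale, a phone measure, is answered after the therapist has explained the rationale of the treatment that this participant will receive, with or without support (Treatment acceptance measures), so that therapist knows the active condition concerned.

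**4. When would this bias a comparison?** Let b₁ and b₂ be the mean shift in FFS score due to the caller in two arms. The bias in the between-arm difference is b₁ − b₂. Table 1 gives one mode for all participants. If the shift is the same in both arms, b₁ − b₂ = 0 and it cancels. If it differs, the difference passes in full into the estimate. The article gives no information on b₁ or b₂. The planned effect is d = 1, so any value assumed for b₁ − b₂ in SD units reappears unchanged as a fraction of the planned effect. Such a figure would only restate the assumption, and none is offered here.

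**The case against.** The best defence is that the article discloses the lack of blinding under its own heading and gives a reason, so a careful reader is not misled, and that no sample size, eligibility rule or analysis rests on the label. That limits the consequence but does not resolve the contradiction: the article makes two statements about blinding and they conflict. This is not a detail left to a fuller protocol.

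Several further objections stand.

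- **The caller.** A reader might infer that the unblinded team, or even the weekly support psychologist, takes the FFS. The article does not say so. The clinical team is tied to screening, the support psychologists to the guidance calls, and a reminder to therapists does not make them assessors. It is probable that the caller knows the arm; it is not stated.
- **Table 1.** It is incomplete: the survey system has no measure, sociodemographic data have no source, and the qualitative interview is absent. How the FFS items are answered in the call is not described.
- **Choice of remedy.** If an assessor or analyst is in fact blinded, the right correction is to name that role. Callers blind to arm would also address interviewer influence while keeping the phone mode.
- **Online collection.** The Discussion notes that psychometric properties may change when assessment is web-based, and it expects dropout of around 30 %, so phone contact may have some value for retention.
- **Clinician-based measures.** A reader might conclude that the Clinician Severity Scale and ADIS-IV should be demoted. They are already a secondary outcome and a diagnostic interview, so a label is enough.

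**Conclusion.** The point holds as a contradiction in the stated design. The article calls the trial simple-blind, says that participants and researchers are not blind, and describes no assessor or analyst who is. This rests on the text alone and is firm.

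The consequence for outcomes is less certain. One of the two primary outcomes, at least two secondary self-report scales, one clinician rating and the diagnostic interview are open to the influence of someone who probably knows the arm. That relies on the inference about the caller, and it biases a comparison only if the influence differs by arm. Its size cannot be derived from the document. The FFQ-II is not exposed to a caller, although, like every self-report measure here, it is exposed to the expectations of participants who know their arm. The document does not support a claim that the FFS result will be biased by any particular amount.

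The limitations in the Discussion mention phone and online measurement as a psychometric matter but not the absence of blinding. The correction should be made; it does not put the trial as a whole in question.

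**What to change.** 1. Reconcile the two sections. Describe the trial as open-label in Study design. If some role is in fact blinded, name it there and narrow the statement under Recruitment, randomization and blinding accordingly.
2. Have participants complete the FFS, the Fear and Avoidance Scales and the Patient's Improvement Scale alone, through the survey system or the program already in use, as is done for the FFQ-II. Use the same mode at every assessment in all arms, and correct the source column of Table 1 to match. If the phone mode is kept, use callers blind to arm and say so.
3. Label the Clinician Severity Scale and the ADIS-IV as unblinded ratings, unless blinded raters are used.
4. Add the absence of blinding to the limitations in the Discussion.

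The cost is a few sentences and some short online forms, with no extra staff for self-completion. Completion may be slightly lower than by phone; the email reminders already planned would help. The web-administration caveat would then extend to the FFS, but the Discussion already accepts it for the measures taken online. None of this removes expectancy among participants who know their arm, in particular those on the waiting list.
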